#### Measures of putative mediators

##### Minnesota withdrawal scale

We monitor withdrawal severity with the Minnesota Withdrawal Scale (MWS), a 10-item scale that is reliable and sensitive [77,78].

##### Anxiety sensitivity index-III

The Anxiety Sensitivity Index-III (ASI-III) is an 18-item measure in which respondents indicate the degree to which they are concerned about possible negative consequences of anxiety-related symptoms [79]. These items were derived from the Anxiety Sensitivity Index (ASI) [25] and the Anxiety Sensitivity Index-Revised (ASI-R) [80]. ASI-III and its subscales show improvements over previous measures of the construct regarding reliability and factorial validity; as well as convergent, discriminant, and criterion-related validity [79].

##### Inventory of depression and anxiety symptoms

The Inventory of Depression and Anxiety Symptoms (IDAS) is a 64-item measure designed to assess specific symptoms of major depression and anxiety disorders [81]. The scales are internally consistent, show excellent convergent validity, and demonstrate good discriminant validity [81].

#### Measures of treatment integrity and acceptance

##### Treatment credibility and expectancy

The Treatment Credibility/Expectancy Questionnaire (CEQ) is a commonly used six-item measure assessing treatment credibility and expectancy [82]. We administer the scale after the first treatment sessions of the ST+CTRL and ST+EX protocols to later examine whether treatment expectancy or credibility varied between the intervention conditions.

##### Therapist adherence

All sessions for CBT and the CTRL interventions are audio-taped and 10% will be rated by independent raters (that is, raters not otherwise associated with the treatment delivery) to assess therapist adherence to and competence with the treatment protocol. Rating checklists and scales were developed for this use.

##### Patient adherence

Patient adherence to the smoking cessation intervention, exercise intervention, and wellness program are assessed by taking attendance at each session (that is, number of total sessions attended). Adherence to the nicotine patch usage is assessed at Weeks 1 to 8 following the quit date. A significant difference in fitness (functional capacity) as expressed in METs between ST+EX and ST+CTRL conditions provides evidence of integrity of the exercise intervention. An assessment team that is blind to study condition will conduct the exercise testing.

##### Adverse events

During the treatment period of the study, the assessment of adverse events occurs at each weekly assessment using standard reporting forms. Participants’ blood pressure (using a brachial artery cuff) and pulse are measured at baseline and at each weekly assessment

##### Concurrent treatment

Use of medications other than nicotine patch, other aids to smoking cessation, and participation in any concurrent psychotherapeutic treatment are assessed at each major outcome assessment (for example, baseline, quit date, weeks 2, 4, 8, 10, 16, and 24 following quit date) point.

##### Treatment dose

Because some of our participants will not attend all treatment sessions, we will include number of treatment sessions received as an additional predictor in our major analyses. If treatment dose has a significant impact on outcomes, we will use the procedures suggested by Aiken and West [87] to determine the level of dosage necessary for a significant treatment effect on abstinence.

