**Methods:**

STEP is a randomized clinical trial that compares a vigorous-intensity exercise intervention to a health and wellness education intervention as an aid for smoking cessation in adults with elevated AS. One hundred and fifty eligible participants will receive standard treatment (ST) for smoking cessation that includes cognitive behavioral therapy (CBT) and nicotine replacement therapy (NRT). In addition, participants will be randomly assigned to either an exercise intervention (ST+EX) or a health and wellness education intervention (ST+CTRL). Participants in both arms will meet 3 times a week for 15 weeks, receiving CBT once a week for the first 7 weeks, and 3 supervised exercise or health and wellness education sessions (depending on randomization) per week for the full 15-week intervention. Participants will be asked to set a quit date for 6 weeks after the baseline visit, and smoking cessation outcomes as well as putative mediator variables will be measured up to 6 months following the quit date.

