#### Baseline/randomization

If deemed eligible after the diagnostic and medical screening visits (based on the inclusion and exclusion criteria presented previously), participants are invited to come in for baseline assessments within 3 weeks. We selected a 3-week window to allow sufficient time to form a cohort/group while also minimizing pre-randomization attrition. Baseline assessments for both conditions include vital signs, height and weight, and a reading of expired air carbon monoxide levels (assessed with a carbon monoxide monitor [62]). Additionally, participants meet their group members, receive an introduction to the study, and are informed of their condition assignment, which takes place after the first group member arrives for the baseline session. The project Biostatistician (DR) oversees the randomization process. Participants are randomized to either the ST+CTRL or ST+EX conditions. Prior to analyzing the data, the project Biostatistician will check the balance of randomization and statistically control for any factors that are imbalanced.

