### STEP interventions

#### Standard treatment for smoking cessation (ST)

All participants receive standard treatment for smoking cessation based on the most recent clinical practice guideline from the US Department of Health and Human Services, Treating Tobacco Use and Dependence [2]. This includes CBT for smoking cessation combined with NRT. This standard treatment is delivered through manualized once-weekly 60-min sessions over a 7-week period (Smoking Cessation Program; Therapist Guide [63]; see Figure 3). Topics discussed include identifying high-risk situations for smoking relapse, self-monitoring of cigarette consumption, identifying maladaptive thoughts and behaviors related to the maintenance of smoking patterns, enlisting social support, and developing coping strategies. The first 5 weeks of the intervention serve as planning and preparation weeks. The first day of week 6 of the study is designated as ‘quit day’, at which point participants are asked to make their quit attempt (see Figure 2). At this time, all participants will be given the option to start NRT. Participants are carefully educated about the proper use of the patch prior to quit day and are instructed to apply one patch daily. Based on the number of cigarettes they are smoking prior to quit day, clinicians offer patients a choice of 21-mg patches (indicated for those smoking >10 cigarettes per day), 14-mg patches (indicated for those smoking 10 or less cigarettes per day), or a 7-mg patch (indicated for those smoking <10 cigarettes per day). They gradually taper to a lower dose of the patch every 2 weeks. All participants are asked to taper off the lowest dose of the patch by week 14, at which time the patch is no longer provided. At each session while using the patch, participants are asked about current side effects they may be experiencing. Again, participants can also elect not to use the patch.

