#### Using a 6-month over a 12-month follow-up

We had several reasons for choosing a 6-month post-quit follow-up over a 12-month follow-up. First, a 6-month follow-up seems reasonable given the well-accepted observation that most smoking relapses occur in the first 3 months post-cessation [89,90]. Second, we want to examine point prevalence abstinence at a number of key time points of interest: 2, 4, 8, 10, 16, and 24 weeks following quit date (see Figure 2 and Table 1). The first two time points reflect our particular interest in immediate vulnerability to relapse as a result of elevated anxiety symptoms. Week 2 also corresponds to the end of the CBT intervention. Week 8 corresponds to the end of nicotine patch usage, Week 10 corresponds to the end of the EX/CTRL interventions, and Weeks 16 and 24 allow for longer-term follow-up. However, it should be noted that we also employ the smoking TLFB interview, which provides information on daily smoking rates over the 6-month follow-up. We previously demonstrated the reliability and validity of the TLFB method for use in assessing adult smoking outcomes [63].

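### Total sessions attended, a post-randomisation variable, enters the major analyses, and the protocol does not say that the comparison by assigned arm without it stays primary

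*Protocol article*

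**What the plan says.** Under Treatment dose, the protocol article notes that some participants will miss sessions and then states that "we will include number of treatment sessions received as an additional predictor in our major analyses". If dose proves to have a significant impact on outcome, cited regression procedures will be used to "determine the level of dosage necessary for a significant treatment effect on abstinence".

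Under Patient adherence, attendance at the smoking cessation, exercise and wellness components is assessed by "taking attendance at each session (that is, number of total sessions attended"). It is therefore a total over the whole programme.

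The timing is fixed elsewhere:
- At baseline, participants "are informed of their condition assignment, which takes place after the first group member arrives for the baseline session". The exercise programme starts one week later.
- The abstract describes "3 supervised exercise or health and wellness education sessions (depending on randomization) per week for the full 15-week intervention".
- Under Standard treatment, "The first day of week 6 of the study is designated as" quit day.
- In the follow-up rationale, "Week 10 corresponds to the end of the EX/CTRL interventions", counted from the quit date.

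Analytic methods describes the GLMM for abstinence and the Cox models for lapse and relapse without an attendance term. The Missing data section presents its pattern analysis as a rerun of the primary analyses. The Treatment dose section has no comparable label.

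**The concern.** Randomisation protects the comparison of arms as assigned. Attendance comes after assignment and may respond to it: treadmill exercise at vigorous intensity and classroom-style wellness sessions make different demands. Attendance may also reflect the motivation that drives quitting, and most of it accrues during the period in which the outcome is being determined. Holding it fixed compares participants in the two arms who ended with the same attendance, and these need not be alike at baseline.

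Three things are at stake:
- The arm coefficient can show an effect where there is none, or hide a real one.
- If exercise helps partly by keeping people in treatment, that benefit is adjusted away.
- In the Cox models, a programme total used as a fixed predictor lets sessions attended after a lapse help explain the time to that lapse.

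The follow-on step then converts a non-randomised attendance gradient and a significance threshold into an apparent dose requirement, although one session is a different treatment in each arm.

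**Working it through.** **1. How much attendance follows quit day.** Exercise or wellness sessions: 3 × 15 = 45. Weeks 1 to 5 give 3 × 5 = 15 before quit day. Weeks 6 to 15 give 3 × 10 = 30, and 30/45 = 67%. The article does not say whether the seven weekly CBT sessions count. If they do, 5 fall before quit day and 2 after, so the share is 32/52 = 62%. The ten post-quit weeks lie inside the three months in which, by the article's own rationale for 6-month follow-up, most relapses happen.

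**2. The Cox models.** Someone who lapses by the end of week 6 still has weeks 7 to 15 ahead: 3 × 9 = 27 of 45 sessions (60%). All 27 can enter the total used to predict a lapse that has already occurred.

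**3. Size for a point-in-time contrast such as 6-month abstinence.** The article has no attendance figure to reproduce, so every attendance input here is an assumption. I used 75 per arm (equal allocation assumed), a two-sided 5% level and 1,500 simulated trials per row. U is a standard normal motivation factor.

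attendance = 30 + shift × arm + 9U + 5e, limited to 0–45

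logit P(abstinent) = −1.6 + arm effect + U

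Logistic regression was fitted with and without attendance. Ranges are across repeated runs.

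| Scenario | Log-OR without sessions | Log-OR with sessions | Rejection without | Rejection with |
|---|---|---|---|---|
| No effect, equal attendance | about 0 | −0.02 to +0.02 | 5% | 5% |
| No effect, ST+EX 4 fewer | about 0 | +0.33 to +0.35 | about 5% | 10–12% |
| No effect, ST+EX 7 fewer | about 0 | +0.55 to +0.62 | about 5% | 22–26% |
| No effect, ST+EX 4 more | about 0 | −0.30 to −0.31 | about 5% | 10–11% |
| No effect, 4 fewer, U not affecting abstinence | about 0 | 0.00 | 4% | 3–4% |
| Real benefit, partly through attendance | 0.52–0.54 | −0.06 to −0.10 | 29–33% | 5–6% |

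On the odds-ratio scale, exp(0.33) = 1.4 and exp(0.62) = 1.9. The last row uses a direct arm effect of 0.4, 6 more sessions in ST+EX and 0.6 on the logit per 10 sessions. The adjusted estimate falls below even the direct 0.4, so two things act at once: the retention benefit is removed, and the shared cause adds bias.

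**4. A second model, in which attendance also falls after relapse.** Control abstinence is 20% as in the Power analyses section; relapse times are exponential with mean 4 weeks after quit day (assumed).
- With no arm difference in attendance, a null odds ratio stays at 0.99–1.02.
- With ST+EX attending about 2.3 to 5.3 fewer sessions, it becomes 1.20–1.46 with a shared cause only, 1.41–2.68 with the relapse effect only, and 1.62–3.72 with both.
- At 150 participants with both, false positives are 17% in the moderate case and 67% in the strong one.

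**5. The slope contrast.** In a null longitudinal check (75 per arm, seven visits, quadratic time, GEE, 400 replicates), sessions were added as a main effect only and ST+EX attended 4 or 7 fewer. The arm-by-time estimate stayed near zero (+0.005 and −0.018), with rejection of 5.8% and 6.5% against 5.0% and 6.2% without sessions. When attendance also fell with smoking, the slope stayed near zero (+0.024 and −0.040; 4.5% and 6.8%), but the week-24 contrast moved by +0.48 and +0.75, with 29% and 57% rejection.

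**The case against.** The best defence is that the dose model was always meant as a supplement. Analytic methods sets out the GLMM and Cox comparisons without attendance and speaks of participants as assigned; Treatment dose is a separate subsection, next to a missing-data section that is clearly a sensitivity analysis. This reading is possible. A reader might infer that the randomised comparison has been abandoned, and the text does not say so. Nor does it say that the comparison is kept as primary: the covariate goes into the major analyses, without the rerun label used in the next section. What is criticised is a stated rule, not a detail left to a fuller plan.

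A reader might also infer that the treatment effect is biased, or that relapsers stop attending and this alone causes the bias. Neither is supported. The article reports no attendance by arm and never says that relapse reduces attendance; that is an inference from timing. With equal attendance and no true effect there was no bias, and attendance that depended on relapse but not on arm left the odds ratio unchanged. The article also matches contact time, partly to limit differential attrition, which may keep attendance similar.

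Finally, the article puts the slope of abstinence first, and the check found no distortion of it when sessions enter as a main effect. This stands and narrows the point. It does not remove it, because the Power analyses section names 6-month abstinence as the primary hypothesis, and lapse and relapse times are also primary-aim outcomes.

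**Conclusion.** The point holds as a defect in the stated rule. A model containing total sessions attended does not estimate the effect of assignment, and the article leaves open whether that model is the main one. The exposed comparisons are 6-month abstinence and the two Cox analyses; distortion of the slope contrast was not shown.

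Direction and size are unknown in advance. Bias needs attendance to differ by arm and also to be tied to abstinence, through shared causes or, if relapse lowers attendance, by that route. Under the assumed inputs of the first model, a deficit of 4 to 7 sessions in ST+EX gives about +0.3 to +0.6 on the log-odds scale with roughly 10 to 25% false positives; a surplus reverses the sign; equal attendance gives none. The larger figures from the second model rest on stronger assumptions. None of these is a prediction for this trial. The conclusion that the primary comparison should not depend on attendance turning out equal needs no simulation.

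**What to change.** - State that the GLMM and Cox comparisons by randomised arm, without sessions attended, are the primary analyses.
- Move the session-dose model to a separate analysis labelled exploratory and non-causal. Use attendance before quit day only, or time-updated attendance counted only up to the outcome, and say whether CBT sessions are included. Even pre-quit attendance is post-randomisation, so the label must stay.
- Drop the search for the attendance level at which the effect becomes significant as a conclusion about required dose. If the gradient is of interest, report it with confidence intervals and by arm.
- Report attendance by arm descriptively.

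The cost is wording in the analysis section. Design, sample size and data collection are unchanged. The change should be made before outcome data are examined by arm.

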##### Missing data

Following the suggestions of Hall and colleagues [83], we will rerun our primary analyses including dummy codes for various missing data patterns (for example, no missing data, sporadic missing, or all missing after a certain time point) to determine if missingness impacts our findings and if the differences between ST+EX and ST+CTRL depend on the missing data pattern (that is, pattern mixture modeling [88]).

##### Power analyses

We performed Monte Carlo simulations to estimate the sample size necessary to detect hypothesized effect sizes in our analyses. Since the mediation analysis has the lowest power, sample size estimates were based on that analysis. We assumed that we would obtain an average of 57% (4 out of 7) of the assessments from the participants. Our Monte Carlo analysis performed 500 simulations, with each simulation computing a bias-corrected bootstrapping analysis of the mediated effects using 1,200 resamples. Results indicate that it would take a sample size of 150 to have a power of 0.80 to detect significant mediated effect if the ‘a’ path has a large effect size and the ‘b’ path has a medium effect size (see Figure 1). Thus, our target sample size was set at 150.

Next, we determined the power for our primary hypothesis that PPA at the 6-month follow-up would be higher in ST+EX than in ST+CTRL. Given the sample size of 150 determined by our mediation power analysis, we calculated the smallest PPA that we could detect with power >0.80. Assuming that the PPA in ST+CTRL will be 20% [60], our Monte Carlo simulations indicate that we will be able to detect a significant difference between ST+EX and ST+CTRL with power >0.80 if the PPA rate in ST+EX is 35% or greater.

### Rationale for key study protocol choices

#### Sample

A key decision was the selection of participants high in AS as opposed to some other anxiety or mood-related risk factor, because of the specific prediction offered by AS across multiple studies (see introduction). High AS is operationalized by an ASI-16 score of ≥20. Also, we chose to study adult daily smokers who are currently motivated to quit because our intervention will not involve any modules (for example, motivational interviewing) designed to increase motivation for cessation. Smokers using other types of nicotine products (for example, smokeless tobacco, cigars) will not be included in the sample, as the study was designed specifically for reducing cigarette smoking. Assessments of cigarette smoking could be confounded by inclusion of other types of nicotine products.

#### Inclusion of nicotine patch in standard treatment

Because recent clinical guidelines recommend that all smokers attempting to quit smoking receive pharmacotherapy [89,90], we believe it is important to make pharmacotherapy available as part of our standard smoking cessation treatment. We selected the transdermal nicotine patch (TNP) because of the extensive empirical literature supporting its effectiveness and safety, its ease of use, and its relatively benign side effect profile, which have led to its approval as an over-the-counter medication. We chose to provide the patch for 8 weeks because use of TNP for longer than 8 weeks does not appear to improve treatment efficacy [91]. Overall, using TNP with standard smoking counseling allows us to examine if the ST+EX is more efficacious than existing (standard) treatment. Because TNP is optional, its use will be tracked for each study participant.

#### Dose, duration, and format of the exercise intervention

We elected to use the public health recommended dose of vigorous-intensity exercise (that is, 75 min of aerobic exercise at >76% of maximum heart rate per week [2]; because: (1) research suggests that it can yield large reductions in AS [54]; and (2) a comparable dose was employed in the [60] study that demonstrated the efficacy of exercise as an aid for smoking cessation. In order to ensure that the exercise intervention is of sufficient duration [57], we decided to match the length of the exercise intervention (that is, 15 weeks) to that of established psychotherapies that show clear efficacy for reducing AS, depressed mood, and anxiety among individuals with elevated levels of AS (for example, cognitive-behavioral treatment of panic disorder; for example, [92-94]). Consistent with the American College of Sports Medicine (ACSM) exercise prescription guidelines [95], participants are encouraged to progress to the study dose during the first 3 weeks (by varying intensity and duration of exercise) of the smoking cessation program. From week 4 (that is, 2 weeks prior to the quit date; see Table 1) to week 15, participants are expected to exercise at the study dose. Finally, participants are required to complete their exercise sessions at the study site’s exercise facility under the supervision of a trained staff member. Our decision to utilize a supervised instead of a combination supervised/home-based format, which may be more attractive from a cost-efficacy perspective, is guided by the specific aims of our study. Specifically, in order to examine the efficacy and mechanisms of exercise for smoking cessation, it is essential to achieve the highest intervention adherence rates possible, which is more easily accomplished using a supervised instead of a combination supervised/home-based format (for example, [60,66]).

#### Inclusion of a control condition

In order to isolate the effects of the exercise intervention, while at the same time reducing the risk of differential attrition, we needed to equate the two conditions for common factors (for example, expectancy effects, demand characteristics, social contact, expert contact). We are accomplishing this by requiring participants who are not assigned to receive the exercise intervention to attend a 15-week Wellness Program. The Wellness Program was developed and previously implemented effectively by our team (for example, [60,66]). Matching the exercise intervention for contact time, participants attend three 45-min sessions each week. Each session (for example, lectures, handouts, films, and discussions) focuses on lifestyle issues, such as healthy eating and prevention of cancer and cardiovascular disease.

